## Introduction

Birth asphyxia accounts for a quarter of a million neonatal deaths world-wide but simple resuscitative measures could reduce mortality and morbidities. Meta-analysis of neonatal resuscitation training (NRT) like the Neonatal resuscitation programme (NRP), Neonatal life support (NLS) and Helping Babies Breathe (HBB) have shown a reduction in perinatal and neonatal mortality when compared with controls. Specifically, NRT decreases the risk of still birth by 21%, 7-day neonatal mortality by 47% and 28-days mortality by 50%. Although there is substantial contribution in reducing mortality by these training programmes, there is a scope to further improvement.

Typically, a resuscitation team commits errors ranging from 23 to 44% during neonatal resuscitation. Errors commonly involve poor airway techniques and not assessing heart rate due to fragmented attention and lack of situational awareness, compromising patient safety during resuscitation. In 2004, a report identified 47 sentinel events contributing to any "any perinatal death or major permanent loss of function unrelated to a congenital condition in an infant with a birth weight >2.5kg". Specifically, the report found the major contributing root causes for sentinel events were poor: (i) staff communication (72%) and (ii) staff competency (47%). Behavioural skills including lack of teamwork and poor communication as common contributing factors. Accordingly, training processes, staff education and communication protocols are key risk reduction strategies where human factors could be one of the modifiable factors in these situations. Many agencies have emphasised the importance of studying human factors during neonatal resuscitation. In spite of the recommendations, there is a dearth of studies in this examining human factors.

## Multi-tasking and situational awareness

Typically, all individuals within the neonatal medical team (including but not limited to junior trainee doctors, advanced neonatal nurse practitioners and senior trainee doctors) who participate in neonatal resuscitation are NLS programme certified. In practice, it is generally assumed the senior person performs tasks in a more optimal manner and may be (informally) designated with the critically important task of managing the patient's airway, acting as "resuscitation leader". This leads to the designated leader having to multi-task. In dynamic, time critical situations such as neonatal resuscitation, multi-tasking may lead to human error,

loss/reduction in situational awareness, ineffective communication, and sub optimal performance. Alternatively, having a dedicated resuscitation leader who has single dedicated role of managing the team/situation could improve overall situational awareness and resuscitation outcomes. For example, a study analysed resuscitation error and concluded that decreasing cognitive and technical load can be an error reducing strategy. Additionally, a team briefing to empower team members during resuscitation by allocating roles/task could further improve situational awareness and overall performance. However, having a stand-alone team leader and use of a team briefing with a standardised checklist is yet to be studied to reduce distractions.

## **Digital technologies: Cause and solution**

Monitoring heart rate, use of pulse oximeter for oxygen saturation, pressure delivered by the resuscitation device (e.g., T piece) and oxygen supply levels are some of the possible multi-tasking requirements during neonatal resuscitation. Previous studies have shown that novice trainees focus more on the monitoring system rather than the patient/baby. Another common issue is task fixation when the user's cognition is impaired by the situation, especially as they are concentrating on a task. Yet, there is no standard or objective methodology for assessing situational awareness but could be inferred by observing human behaviours.

Wearable eye-tracking glasses have been used in aviation industry to study visual attention (VA). Wearable eye-tracking glasses have two cameras, one capturing the reflected infra-red light tracking pupillary movement and another camera capturing video from the participant's viewpoint. This wearable device could provide details on participants visual fixation, gaze shifts (saccades) and regression/lookback (a saccadic movement) whereby the user returns to the task after a distraction. Those eye-tracking data could provide objective and reliable information pertaining to area of interest (AOI), time spent on each AOI and number of gaze shifts/saccades during neonatal care. The videos captured by the eye-tracker could also help with the appreciation of the situational context and debriefing the scenario.

## **Eye-tracking devices/glasses in medicine**

Eye-tracking is a method of observing an eye movement as a reflection of attentional behaviour. It is based on the concept that attention is focused to a particular location to

maintain attention on a point of interest. This concept is utilized in eye-tracking technology to capture gaze behaviour, which provides information about an individual's attention over points of interest and allocation over time. In recent years, it has been used in medical field and is a valuable tool in medical education by providing training and effective feedback.

To date, wearable eye-tracking glasses have been used in few neonatal and critical care studies. For example, modern wearable eye-tracking glasses have been assessed for usability in a delivery room simulation where focus of cognitive attention was successfully captured, and all wearers agreed they would wear the glasses during the resuscitation. Equally, those findings were replicated in another neonatal simulation study where eye-tracking glasses did not provide any discomfort and participants felt the technology easy to use during the simulation. Attempts to examine human factor have been investigated during neonatal intubation in the neonatal unit, which found 50% of visual attentions is directed away from the infant and the team when they used nonstandard communication. This highlights how eye-tracking device could be an effective tool to analyze human factors for improved medical training, but the study failed to examine task-cognitive load with presence of dedicated team leader and outcomes with use of structured checklist.

We hypothesize that there will be difference in situational awareness, workload, and performance when there is multi-tasking as compared to performing single dedicated role during neonatal care. Here we propose the use of wearable eye-tracking glasses to help standardise approaches to examine situational awareness inferred by objective data from examining human factors/behaviour. Additionally, this may help inform the impact of using standardised checklist and role allocation on multi-tasking, which will be useful in resource limited settings. Subsequently, this manuscript describes the protocol that will be used to evaluate these approaches in a pilot observational study.

#### Primary aims:

To compare the VA of a team operator/member when s/he:

- 1) Is managing airway and acting as team leader and
- 2) Has a dedicated team leader.

#### Secondary aims:

To examine impact of a team briefing prior to resuscitation on:

- 1) Team performance using the validated modified neonatal resuscitation performance evaluation (NRPE) tool, when (i) the operator is managing both airway and acting as team leader, compared to (ii) having a dedicated team leader with checklist.
- 2) Compare the workload with or without a team leader and standardised checklist. We will use National Aeronautics and Space Administration task load index (NASA-TLX) for assessing the workload.

## **Materials and methods**

### **Study**

The clinical research question according to the patient, intervention, comparison, outcome, and time (PICOT) process is as follows:

- P: Neonatal resuscitation simulation scenarios, (i) preterm and (ii) term.
- I: Having dedicated airway operator and dedicated “resuscitation leader” (with and without a pre-briefing).
- C: Operator is managing both airway and acting as “resuscitation leader” (with and without a pre-briefing).
- O: Visual attention evaluated by eye-tracking, team performance and workload.
- T: Observational study in a simulation-based model.

### **Design**

We aim to design a single centre, simulation-based, observational study utilising eye-tracking tools for visual attention assessment. The protocol was developed according to the Standard Protocol Items: Recommendations for Interventional Trials’ (SPIRIT) checklist as appropriate, Figure 1. As this is a study protocol, no data has been included and conforms to PLOS data policy.

<Figure 1, see end of document>

### **Study settings**

This study will be conducted in regional level-3 neonatal hospital at James Cook University Hospital (South Tees Hospital NHS Foundation Trust), Middlesbrough, UK. Our center has approximately 6000 deliveries with 400 admissions each year. The entire simulation study will be run in a dedicated immersive simulation suite providing standard delivery room equipment and environment.

## **Recruitment**

An ethics application was submitted to IRAS and approved April 2022 (reference number: 314695). Written, informed consent to participate will be obtained by all participants prior to each stage of the study in accordance with General Data Protection Regulations (GDPR). Those interested will then be given a Participant Information Sheet (PIS) concerning the study with consent form (See Appendix-1). All participants will be allowed to withdraw from the study at any time. The individual identity will not be used for any data analysis and reporting.

## **Participants**

Neonatal staff from James Cook Hospital will be invited to participate between April 2022 and August 2022. Participants will not be stratified according to any variable (e.g., age, gender). All nursing and paediatric trainees need to complete Neonatal life support course every 2 years.

Inclusion criteria include:

1. For medical staff: must be paediatric trainee (any level) who has worked at least 6 months in neonatal intensive care settings.
2. For nurse practitioners: must be currently working in neonatal unit for at least 6 months or more.
3. For nursing staff: must be staff currently working in the neonatal unit.
4. Must have valid NLS certification (completed NLS within the last 3 years).
5. Must have participated or observed one neonatal simulation.
6. Must provide written informed consent.

Exclusion criteria include:

1. Not willing to wear eye tracking device.

**Team selection:** Communications will be via email to recruit interested participants (including nurses, nurse practitioners and doctors). Team selection will occur a few weeks prior to the simulation and will be randomly chosen by placing all written participant names in sealed envelopes and pulled from a ballot box. Teams will have an equal distribution of roles (nurse/tier-1/tier-2) making sure that each consists of:

- i. One neonatal nurse,
- ii. One tier-1 trainee (senior house officer working as tier-1 with 1-3 years paediatric training or advanced neonatal nurse practitioners working as tier-1) and
- iii. Two tier-2 trainees (senior doctors with  $\geq 3$  years of paediatric training or nurse practitioners working as tier-2).

## **Outcomes: Primary and secondary**

The primary outcomes of this study are the proportion of participants who have altered VA behaviours defined by the objective eye-tracking data (e.g., saccades and fixations). Secondary outcomes are related to the change in team performance and workload due to impact of a team lead with a standardised checklist.

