### *Visual attention*

During each simulation participant visual attention will be objectively assessed with a wearable eye-tracker, as previously described.

*Table S2: Visual attention outcomes*

|                                        | All scenarios
(Between participant comparison) |        |        | Within team post comparison
(Same person comparison) |        |        |
|----------------------------------------|---------------------------------------------------|--------|--------|---------------------------------------------------------|--------|--------|
|                                        | Nurse                                             | Tier-1 | Tier-2 | Nurse                                                   | Tier-1 | Tier-2 |
| AOI (description)                      |                                                   |        |        |                                                         |        |        |
| Time on AOI (seconds)                  |                                                   |        |        |                                                         |        |        |
| Time-to-first fixation (seconds)       |                                                   |        |        |                                                         |        |        |
| Saccades (mean and variability)        |                                                   |        |        |                                                         |        |        |
| Fixations (mean and variability)       |                                                   |        |        |                                                         |        |        |
| Smooth pursuits (mean and variability) |                                                   |        |        |                                                         |        |        |

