## **Study algorithm**

Each team will participate in two simulation scenarios (i) term and (ii) preterm. With 3 teams, there will be total of 6 simulation experiments. Each team will undergo one scenario with a team leader and another scenario without a team leader. The sequence in which each team is allocated with/without team leader would be alternating with each team. For example, if team #1 starts with team leader for their preterm scenario, team #2 would participate same preterm scenario without team leader. This will ensure that both scenarios have an equal number of scenarios with and without a team leader.

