## Sample size

In a previous study using eye tracking glasses examining VA during neonatal resuscitation, in which the operator acted both as an airway manager and team leader. In this study operator spent 35% (SD 8) of time focused on the infant. With the presence of dedicated resuscitation leader, to improve the VA on the infant to 55% with 80% power and alpha error of 0.05, we will need to conduct 6 scenarios with 3 samples in each group (equalling 18 participants).

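### The primary outcome is an undefined proportion of participants with altered attention, while the aim, sample size and analysis concern the operator's mean gaze, and Table S2 shows neither

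*Protocol*

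**What the plan says.** **Primary aims.** The aim begins "To compare the VA of a team operator/member when s/he" and then sets two conditions against each other: managing the airway while also leading, and working with a dedicated leader.

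**Outcomes: Primary and secondary.** The definition given is: "The primary outcomes of this study are the proportion of participants who have altered VA behaviours defined by the objective eye-tracking data". Saccades and fixations follow as examples. The sentence does not say what counts as altered, in which direction, or on which measure. Time on the infant is not mentioned.

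**Sample size.** The calculation cites a previous eye-tracking study: "In this study operator spent 35% (SD 8) of time focused on the infant". The target is "to improve the VA on the infant to 55% with 80% power and alpha error of 0.05", and the result is 3 per group in 6 scenarios.

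**Study algorithm.** "Each team will undergo one scenario with a team leader and another scenario without a team leader". There are three teams.

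**Statistics.** Means and ranges come first, then independent t-tests. No method for a proportion is given, and no variable is tied to the t-tests.

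**Visual attention, Table S2.** The columns are nurse, tier-1 and tier-2, once for a between-participant comparison and once for a same-person comparison. The rows are an area-of-interest description, time on each area, time to first fixation, saccades, fixations and smooth pursuits.

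**The concern.** The primary outcome should be the quantity that answers the aim, justifies the size and receives the main analysis. Here the outcome is a yes/no status per participant, while the sizing variable is a continuous measurement on one role. The variable used to justify the study is therefore not its primary outcome, and the stated primary outcome has neither a size justification nor a planned test.

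The undefined word makes this worse. Two eye-tracking recordings of the same person will almost never agree exactly. Without a threshold nearly everyone is altered, and with one, the threshold fixes the answer. Without a direction, a gain and a loss of attention on the infant count alike. If the threshold and the measure are chosen after the recordings are seen, the headline result is a choice made by the analyst.

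**Working it through.** **1. The Protocol's own figure.** Inputs from Sample size: means 35% and 55%, so difference d = 20 points; SD 8; 80% power; alpha 0.05, taken as two-sided because sidedness is not stated. By the normal approximation:

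n per group = 2 × (1.960 + 0.842)² × 8² / 20² = 2 × 7.85 × 0.16 = 2.51, rounded up to 3.

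This reproduces the stated 3 per group, so the study was sized for a difference of two means of percent gaze time.

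**2. Could it have been a calculation for a proportion of participants?** Reading 35% and 55% that way, with average 45%:

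n per group = [1.960 × √(2 × 0.45 × 0.55) + 0.842 × √(0.35 × 0.65 + 0.55 × 0.45)]² / 0.20² = (1.379 + 0.580)² / 0.04 = about 96.

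The stated 3 cannot have come from that.

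**3. The sections side by side.**

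| Section | Variable | Whose | Contrast |
|---|---|---|---|
| Primary aims | visual attention, no measure named | operator or member | with vs without dedicated leader |
| Primary outcome | share with altered behaviour | participants | none in the sentence |
| Sample size | mean percent of time on the infant | operator | 35% vs 55% |
| Statistics | means, ranges, t-tests; variable not named | 24 participants in 4 teams | independent groups |
| Table S2 | six rows, none a proportion | staff grades | between-participant and same-person; no leader columns |

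Table S2 also has no airway-operator column, and the Protocol text does not say which grade takes the airway. The Briefing section mentions only airway operators being briefed on and testing the eye-tracker, whereas Table S2 expects gaze data for every grade.

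**4. How far the cut-off decides the result (illustration).** Assume normally distributed within-person changes in percent time on the infant, with mean 20 points and SD 8. The SD of a change is 8 when each condition has SD 8 and the correlation is 0.5, since 8 × √(2 × 0.5) = 8. The cut-offs are chosen for illustration.

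- Above 10 points: Φ((20 − 10)/8) = Φ(1.25) = 89%.
- Above 20 points: Φ(0) = 50%.
- Above 30 points: Φ(−1.25) = 11%.

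With no true effect (mean 0) and a 10-point cut-off in either direction, 2 × Φ(−1.25) = 21% would still count as altered. With a true fall of 20 points the figure is again 89%, the same as for a rise.

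**5. Power if the sized variable becomes primary.** Two-sided alpha 0.05, noncentral t distribution.

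- Independent t-test, 3 per group: noncentrality 20 / (8 × √(2/3)) = 3.06, 4 degrees of freedom, critical value 2.776; power 64%. The normal approximation gives 86% (Φ(3.06 − 1.96)), which explains why 3 looked sufficient. Four per group give 84%.
- Paired t-test, 3 pairs: SD of the difference = 8 × √(2(1 − r)), noncentrality = 20 × √3 / SD of the difference, 2 degrees of freedom, critical value 4.303.

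| r (assumed) | SD of difference | Noncentrality | Power |
|---|---|---|---|
| 0 | 11.31 | 3.06 | 40% |
| 0.5 | 8.00 | 4.33 | 62% |
| 0.7 | 6.20 | 5.59 | 79% |
| 0.8 | 5.06 | 6.85 | 90% |

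**The case against.** The best defence is that the outcome sentence should be read with the rest of the Protocol. The aim, the PICOT list and the study algorithm all supply the contrast, and Table S2 has a same-person half, so altered can be taken to mean changed between the two conditions. Time on each area of interest is collected, with the baby listed first, and has its own row in Table S2. A cut-off could be left to a statistical analysis plan, and the study calls itself a pilot and exploratory.

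Much of this stands. A reader might infer that the Protocol contains no comparison at all, or that the outcome rests on saccades and fixations alone. Neither is supported: the contrast is given elsewhere, and those two measures are only examples.

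Three further inferences are tempting and should not be made.

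- **Dilution from the single tier-2 column.** Teams have two tier-2 members, but nothing says that the dedicated leader is one of them or that leader and operator values will be averaged.
- **A family-wise false-positive rate from the rows of Table S2.** The first row is descriptive, the others come from one gaze record and are not independent, and the Statistics section sets no significance threshold for them.
- **A proportion that can move only in thirds.** That counts three operators, whereas the outcome sentence counts participants: 12 from three teams of four, or the 18 and 24 given in Sample size and Statistics.

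The defence does not remove the mismatch itself. An analysis plan can supply a threshold, but it cannot turn a stated yes/no outcome into the continuous one used for sizing without overriding the Protocol. The exploratory label does not cover an 80% power claim for one named variable.

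**Conclusion.** The point holds. As written, the stated primary outcome does not match the aim, the sizing variable or the planned analysis, and its value depends on a threshold that the Protocol does not set. It would be too strong to say that a proportion could never address the aim: defined as within-person change in a stated direction it could, but it would lose the size of the change and is not what was powered.

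Naming the sized variable as primary restores consistency but not the power claim. The figures of about 64% (independent test) and about 40% to 62% (3 pairs, r from 0 to 0.5) assume SD 8 in each condition, normality and a true 20-point difference. The correlation is not given in the Protocol; 80% with 3 pairs needs r slightly above 0.7. The independent-test figure also treats the two runs of a team as unrelated. Each team's two runs use different scenarios, term and preterm, so a high within-pair correlation should not be taken for granted.

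**What to change.** 1. Restate the primary outcome as the percent of recorded scenario time during which the airway operator's gaze is on the infant, compared with versus without a dedicated leader.
2. Make all other eye-tracking measures secondary and descriptive.
3. Lay out Table S2 by role (airway operator, leader, other members) and by condition (with and without a dedicated leader).
4. State before the first simulation whether the same person is airway operator in both runs. If so, report the within-operator difference and replace the independent t-test with a paired analysis.
5. Correct the power statement to what 3 per group or 3 pairs provide, with the assumed SD and correlation.

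**Cost.** Items 1 to 3 change wording and one shell table and use gaze data already planned. Item 4 affects how roles are assigned, so it concerns conduct as well as wording and must be settled before data collection. Item 5 means giving up the 80% claim at the present size. Made after the recordings are seen, the same changes would be a post hoc choice of primary outcome.
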